### Participant timeline

See table 3 for the participant timeline.

**Table 3 T3:** Participant timeline

Activity/ assessment	Approx. time to complete	T_-1_ Prestudy screening/ consent	T_0_ Prestudy randomisation	T_1_ Preintervention	T_2_ Intervention	T_3_ Postintervention tests	F_1_ Follow-up 1 week
Informed consent	5 min	X					
Screening with DASS	5 min	X					
Randomisation	15 min		X				
Baseline assessment— questionnaires	15 min			X			
Baseline assessment— physiological	15 min			X			
Intervention	30 min				X		
Postintervention questionnaires	15 min					X	
Postintervention physiological	15 min					X	
Telephone interview	30 min						X

DASS, Depression Anxiety Stress Scale; F, follow-up; T, timepoint.

### Sample size

The study will aim to recruit 32 participants. This number of participants is generally deemed sufficient for feasibility studies^48^ and would represent approximately 10% of the sample size required in a full trial.^49^ This sample size also falls within what is practical given the available resources.

### Recruitment

Recruitment at the university is being conducted by advertising in communal spaces with posters. Additionally, social media will be used for recruitment by reaching out to mental health support groups and sharing an advertisement for the study on various social networks (note: this recruitment work has begun). Participants will contact the research team if they are interested in taking part. They will then be given an information sheet to read and a consent form to sign. Following this, they will complete the DASS to complete to determine their eligibility regarding mental health symptoms. The cut-off scores for mild to moderate will be defined as follows: depression=10–20, anxiety=8–14 and stress=15–25.^50^ If eligible they will be invited to take part in the intervention. If they display severe mental health symptoms, they will not be invited to take part further and signposted to the relevant mental health services and charities.

## Methods: assignment of interventions

### Allocation

#### Sequence generation

Thirty-two participants will be randomly assigned to one of the four conditions using a computerised random number generator. Permuted block randomisation will be used to ensure that equal numbers of participants are in each condition. The block sizes will not be disclosed to help ensure concealment and prevent any potential prediction of group allocation. This will be conducted by the principal investigator (PI) of the study [name], while the outcome assessor [name] is blinded to this randomisation process.

#### Concealment mechanism

Allocation concealment will be ensured using sequentially numbered, sealed opaque envelopes which contain the group assignment. The PI will carry out the allocation concealment, and ensure that the outcome assessor is blinded to the intervention allocation.

#### Implementation

All participants who provide informed consent and who meet the eligibility criteria will be randomised into a study condition (as described in section Sequence generation). The randomiser [name] will not be directly involved in the recruitment or data collection, and instead, the outcome assessor will conduct the recruitment. The list of random numbers that correspond to group allocation will not be revealed to the researcher ([name]) involved in data collection or recruitment. The sealed envelopes will contain a randomisation number and corresponding intervention identity code for the allocation of participants into the intervention groups. The osteopathic practitioner will then be able to open the envelope and determine which intervention is to be delivered on the day the study is conducted.

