### Analysis of population and missing data

The study will operate on an intention-to-treat basis. All participants randomised and with preintervention data will be included in the final analysis. Any participants with missing data will be included in the analysis using the multiple imputation feature of SPSS.

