### Consent

Participants will scan a QR code on recruitment posters or click a link via email/social media adverts that will take them to the study’s information sheet. The information sheet emphasises that participation is voluntary and that they can withdraw from the study at any stage, without needing to provide a reason. If they have any questions or concerns at this stage, they are encouraged on the information sheet to contact the research team. If they are willing to proceed, they will complete an online consent form (see online supplemental material 3).

10.1136/bmjopen-2023-071680.supp3Supplementary data

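### Table 3 places randomisation before the baseline visit, so a randomised person who never reaches baseline leaves an analysis described as intention-to-treat, and the equal arms are lost

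*Protocol article*

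**What the plan says.** **Order of steps.** In Participant timeline, Table 3 has consent and DASS screening at T-1. A separate 15-minute step follows, headed "T_0_ Prestudy randomisation". The baseline questionnaires and physiological measures come next, under "T_1_ Preintervention".

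**Trigger.** Implementation states: "All participants who provide informed consent and who meet the eligibility criteria will be randomised into a study condition". Neither attendance nor baseline data is a condition. The Consent section shows that consent needs no visit: "If they are willing to proceed, they will complete an online consent form". Under Recruitment, the DASS follows consent, and eligible people are then invited to take part.

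**Number and balance.** Sequence generation says: "Thirty-two participants will be randomly assigned to one of the four conditions using a computerised random number generator". It adds: "Permuted block randomisation will be used to ensure that equal numbers of participants are in each condition".

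**Analysis set.** Analysis of population and missing data describes the study as intention-to-treat, then says: "All participants randomised and with preintervention data will be included in the final analysis". Additional outcomes describes a further question about neck pain and headache, beyond the initial screening, and removes from the analysis anyone who presents with either.

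**Opening the envelope.** Implementation says that the osteopath can "open the envelope and determine which intervention is to be delivered on the day the study is conducted". Blinding gives the order of the visit as baseline measures completed, outcome assessor leaves the room, intervention begins. It does not say where in that order the envelope is opened.

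**The concern.** Under Table 3 a person can be allocated after an online consent form and a screening questionnaire, without having attended. If that person does not come, an allocation has been made, no preintervention data exist, and the stated analysis set leaves the person out. Three things are then at stake.

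- The set analysed is not everyone randomised, although the plan calls it intention-to-treat.
- The permuted blocks no longer deliver the equal arms they are there to ensure. With 8 per arm, two absences cost a quarter of an arm.
- People found to have neck pain or headache after T0 are also removed once randomised, which adds to the same loss.

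The order also hides useful information. Non-attendance after screening is something a feasibility study should count, and it is cleaner to count it before allocation than as loss from the randomised set.

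**Working it through.** **Inputs from the article.** 32 randomised (Sample size; Sequence generation) in four equal arms, so 32/4 = 8 per arm. The Abstract says 30, which would give 30/4 = 7.5, so 32 is used here. The 32 rests on a feasibility norm and a share of a full trial. No power calculation is given, so there is none to reproduce.

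**Input not in the article.** The probability r that a randomised person does not reach T1. I assume 5%, 10% and 20%, independent between people and equal across arms.

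**Step 1: a fixed number k of absences among 32.** The arms stay equal only if k is a multiple of 4, with probability C(8, k/4)^4 / C(32, k).

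- k = 1, 2 or 3: probability 0.
- k = 4: 8^4 / 35,960 = 4,096 / 35,960 = 0.114.
- k = 8: 28^4 / 10,518,300 = 614,656 / 10,518,300 = 0.058.

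**Step 2: an assumed rate r.**

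- Mean number analysed = 32(1 - r).
- P(all 32 attend) = (1 - r)^32.
- P(arms equal) = sum over j = 0 to 8 of [C(8, j) r^j (1 - r)^(8-j)]^4.
- P(a given arm keeps 6 or fewer) = q = 1 - (1 - r)^8 - 8r(1 - r)^7, which is 0.057, 0.187 and 0.497. For at least one of four arms it is 1 - (1 - q)^4.
- Number to randomise so that 32 are analysed on average = 32/(1 - r), rounded up.

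| Assumed r | Mean analysed | P(all attend) | P(arms equal) | P(some arm 6 or fewer) | To randomise for 32 |
|---|---|---|---|---|---|
| 5% | 30.4 | 0.19 | 0.20 | 0.21 | 34 |
| 10% | 28.8 | 0.034 | 0.056 | 0.56 | 36 |
| 20% | 25.6 | 0.0008 | 0.021 | 0.94 | 40 |

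By simulation of four binomial arms, the mean size of the smallest arm is 7.0, 6.3 and 5.2.

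**Step 3: what imbalance costs in precision.** If one arm falls from 8 to 6, the standard error of a simple contrast with an arm of 8 is multiplied by sqrt[(1/8 + 1/6)/(2/8)] = sqrt(1.167) = 1.08, a rise of about 8%.

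**Step 4: the same study with allocation after T1.** A person who does not attend uses no allocation. 32 allocated means 32 with preintervention data, 8 per arm. Only exclusions made after allocation, such as neck pain or headache arising during the session, could still unbalance the arms.

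**The case against.** **The envelope procedure may already protect the allocations.** The envelopes are sequentially numbered and opened by the osteopath on the study day. If the next one is opened only for someone who attends, an absentee uses none, and T0 could mean no more than preparation of the list. This is a fair reading, so it cannot be taken as fact that each absentee consumes one of the 32 allocations. But Table 3 and the consent-plus-eligibility trigger say otherwise, and the two accounts need reconciling.

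**Bias in the baseline.** A reader might infer that unblinded participants complete the baseline self-reports already knowing their arm, which would bias every pre-post comparison. The article does not support this. Its visit order has the baseline completed and the assessor out of the room before the intervention begins. Disclosing the arm earlier would defeat the assessor's blinding. What remains is that the text suggests a later opening without stating it.

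**Selection bias.** A reader might also infer that losing people before T1 biases the comparison of arms. The envelope stays sealed until the study day, so someone who never attends has no evident way to know the arm. Such losses cost size and balance.

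**Scale.** The rates are assumed, and an 8% wider standard error changes little in a study whose primary outcomes are feasibility and acceptability and which admits low power. Nothing bars randomising more people: the recruitment criterion of more than 100 responders, at least half eligible, would give over 50 candidates. All of this stands and keeps the point modest. It does not remove the conflict between the stated order, the analysis set and the intention-to-treat label.

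**Conclusion.** The point holds as a correctable fault in a stated order of events. Table 3 and Implementation place randomisation before baseline, and the analysis set then leaves out randomised people without baseline data. On that order any one, two or three absences are certain to break the equal arms. The expected harm is a modest loss of size and balance. At an assumed 10% non-attendance, about 29 of 32 would be analysed, with a 6% chance of equal arms. At 5% the figures are about 30 and 20%, and at 20% about 26 and 2%. These figures assume independent absences at a common rate, no replacement, and Table 3 read as written. If envelopes are in fact used only for people who attend, the loss from non-attendance disappears and the fault is a contradiction between Table 3 and the envelope procedure. Bias in the baseline is conditional on an early opening that the article neither describes nor rules out, and should not be claimed.

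**What to change.** 1. In Table 3 and Implementation, place allocation after T1. The practitioner opens the next sequentially numbered envelope only when the baseline questionnaires, physiological measures and preintervention checks (including the neck pain and headache question) are complete and the outcome assessor has left the room.
2. In Analysis of population and missing data, define the analysis set as all randomised participants. With allocation after T1, the condition on preintervention data is no longer needed to deal with non-attendance, and the intention-to-treat label becomes accurate on this point.
3. Reconcile the exclusion in Additional outcomes with that set. This includes symptoms that arise during the session: Modifications adapts the intervention for such participants, while Additional outcomes would drop people presenting with the same symptoms from the analysis. Moving the envelope cannot settle those cases.
4. Report the number lost between screening and allocation as feasibility data.

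Cost: wording in Table 3 and three sections. The envelopes, the practitioner and the day stay the same, with no extra staff or procedures.

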### Blinding (masking)

The outcome assessor will be blind to the participant’s group allocation. After preintervention psychometric and psychophysiological measures (see sections Psychological outcomes and Physiological outcomes, respectively) have been completed, the outcome assessor will leave the room (to ensure blinding) and the intervention will begin, conducted by the osteopath. Participants will not be blinded to study intervention, as the osteopathic practitioner will need to explain study and intervention procedures, in line with the osteopathic practice standards and ethical consent.^13^ The practitioner will not be blinded to the intervention type (as they need to know what intervention to deliver) but will be blinded to the study outcomes. The outcome assessor will also be conducting the data analysis, and the random numbers corresponding to each group will only be revealed when this analysis has been completed. To ensure participants do not disclose the condition they were allocated to, they will be asked not to communicate directly to the outcome assessor about the intervention they received. The study will therefore be single-blinded, where the outcome assessor is blind to intervention allocation, and the osteopathic practitioner will not be blind (hence single-blind).

### Emergency unblinding

As the practitioner is not blinded, no emergency unblinding procedures are deemed necessary.

## Methods: data management and analysis

### Data management

All data will be entered electronically at the university where the data are being collected and kept in a password-protected folder, which only the outcome assessor will have access to for the duration of the study. The electronic data will be kept confidential, and participants’ names will not be linked to their datasets. For the longer term, electronic datasets will be kept indefinitely in the interest of transparency to fulfil any requests for the original data and maintained on the OSF.

## Statistical methods

### Outcomes

Statistical analysis will be conducted using IBM SPSS (V.27). Means and SD will be reported for demographic data that includes gender, age and ethnicity. For the main analysis, data will first be examined for normality using the Shapiro-Wilk test. If data are skewed, logarithmic transformation will be used, otherwise, analysis will continue without any transformation. HRV data will be preprocessed, and inspected for any potential artefacts, and these will be removed if identified. RMSSD will be calculated on the preprocessed artefact removed data using Kubios V.3.5 (https://www.kubios.com/) via Matlab V.R2021a. IAc will then be calculated using the formula: IAc=1/4 Σ [1−(|recorded heartbeats−counted heartbeats|/recorded heartbeats)]. The psychometrics will be totalled according to the relevant questionnaire instructions and subscales.

The main analysis will comprise of seven separate mixed design two (preintervention and postintervention) by four (AVHT, STM, CST, combination (please see: Interventions section for full details of these interventions.)) analysis of covariance (ANCOVA) models. This will comprise of five separate ANCOVAs for the five psychometrics (DASS, PANAS-SF, AAQ, SACS, MAIA) and another two ANCOVAs for the physiological measures of IAc and HRV (as measured by RMSSD and LF/HF ratio). Covariates will consist of (1) whether participants are currently receiving psychotherapy (yes or no) and (2) whether participants are receiving pharmacological treatment (yes or no). Significant models will be examined further using post hoc Bonferroni tests.

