##### Mental health

###### Depression, Anxiety and Stress Scale

The DASS^38^ is a self-report measure made up of 21 items with three subscales that measure depression, anxiety, and stress. The DASS will also be used as a screening tool to identify eligible participants in terms of the severity of mental health symptoms. Examples of items include ‘I couldn’t seem to experience any positive feeling at all’ for the depression scale, ‘I felt I was close to panic’ for the anxiety scale and ‘I found myself getting agitated’ for the stress scale. These are then rated on a four-point Likert scale ranging from 0 (never) to 3 (almost always). Higher scores indicate higher levels of depression, anxiety and stress. The subscales have good internal reliability as measured by Cronbach’s alpha coefficients (α), which are 0.88 for depression, 0.82 for anxiety and 0.90 for stress, as well as 0.93 for the total score.^39^

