###### International PA and NA schedule-short-form

The International Positive and Negative Affect Schedule-Short-Form (PANAS-SF)^40^ is a short-form version of the PANAS and uses 10 items to measure two subscales of PA and NA. Participants are asked to what extent they have felt certain states or emotions, such as ‘inspired’ for the PA scale and ‘upset’ for the NA scale. These are then rated on a five-point Likert scale ranging from 1 (very slightly or not at all) to 5 (extremely). Higher scores indicate higher levels of PA and NA. Both the PA and NA subscales have good internal reliability with both having a Cronbach’s α of 0.84.^40^

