##### Psychological flexibility

###### Acceptance and Action Questionnaire-II

The Acceptance and Action Questionnaire-II (AAQ-II)^41^ is a self-report measure made up of seven items that measures psychological inflexibility or as it is also referred to, experiential avoidance. Items include a list of statements such as ‘I’m afraid of my feelings’ and ‘worries get in the way of my success’. These items are then rated on a seven-point Likert scale from 1 (never true) to 7 (always true). Scores are then totalled with higher scores indicating greater levels of psychological inflexibility and experiential avoidance. The AAQ-II has good internal reliability with a Cronbach’s α of 0.84.^41^

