##### Interoceptive awareness

###### Multidimensional Assessment of Interoceptive Awareness Version 2

The Multidimensional Assessment of Interoceptive Awareness Version 2 (MAIA-2)^43^ is a 37-item self-report measure of interoceptive awareness. The MAIA-2 uses eight subscales which are (1): noticing, for example, ‘when I am tense, I notice where the tension is located in my body’,^1^ not-distracting, for example, ‘I distract myself from sensations of discomfort’,^2^ not-worrying, for example, ‘when I feel physical pain, I become upset’,^3^ attention regulation, for example, ‘I can pay attention to my breath without being distracted by things happening around me’,^4^ emotional awareness, for example, ‘I notice how my body changes when I am angry’,^5^ self-regulation, for example, ‘when I feel overwhelmed I can find a calm place inside’,^6^ body listening, for example, ‘I listen for information from my body about my emotional state, and^7^ trusting, for example, ‘I trust my body sensations’. The items are rated on a six-point Likert scale ranging from 0 (never) to 5 (always). The scales have good internal reliability with the Cronbach’s alpha coefficients for the scales being: 0.64 for noticing, 0.74 for not-distracting, 0.67 for not-worrying, 0.83 for attention regulation, 0.79 for emotional awareness, 0.79 for self-regulation, 0.80 for body listening and 0.83 for trust.^43^

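### The rule to log-transform any skewed outcome cannot be followed for DASS, MAIA-2 or IAc values at or below zero, and would worsen left skew

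*Protocol article*

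**What the plan says.** Statistical methods (Outcomes) states that for the main analysis "data will first be examined for normality using the Shapiro-Wilk test", and then: "If data are skewed, logarithmic transformation will be used, otherwise, analysis will continue without any transformation". No direction of skew, added constant, reflection or alternative method is given, and no outcome is exempted. The main analysis covers DASS, PANAS-SF, AAQ-II, SACS, MAIA-2, IAc and HRV (RMSSD and LF/HF ratio).

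The scales differ in where they start:
- DASS items are "rated on a four-point Likert scale ranging from 0 (never) to 3 (almost always").
- MAIA-2 items are "rated on a six-point Likert scale ranging from 0 (never) to 5 (always").
- PANAS-SF, AAQ-II and SACS items all start at 1; AAQ-II items, for example, are "rated on a seven-point Likert scale from 1 (never true) to 7 (always true").

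IAc is the average over four trials of one minus the relative counting error. On missing values, Analysis of population and missing data says: "Any participants with missing data will be included in the analysis using the multiple imputation feature of SPSS".

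**The concern.** A log transformation suits positive, right-skewed data. The protocol applies it to every outcome judged skewed, including some for which the log does not exist at values that can be observed, and one whose upper bound makes left skew plausible.

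An analyst who follows the text would have to improvise where zeros occur. Valid observations might be lost, or a constant might be chosen after the data are seen. For DASS, the affected participants would be those with the fewest symptoms, so the loss would not be random. The Discussion in the abstract offers the effect sizes as preliminary evidence, with results to inform a later randomised trial, so the scale on which they are estimated should not depend on choices made during analysis.

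**Working it through.** The protocol states no figure on this point, so there is none to reproduce. The check follows the rule through the protocol's own scales and formula.

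**1. Lowest possible scores** (number of items × lowest item value)
- DASS subscale or total: 0. MAIA-2 subscale: 0.
- PANAS-SF subscale: 5 × 1 = 5. AAQ-II: 7 × 1 = 7. SACS total: 10 × 1 = 10.

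Only DASS and MAIA-2 can reach 0, where the log is undefined. Under Eligibility criteria and Recruitment, one DASS domain in range is enough (depression 10–20, anxiety 8–14 or stress 15–25). The DASS total at screening is therefore at least 8, but another subscale can be 0, and any score can fall after the intervention.

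**2. Limits of IAc**

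With R recorded and C counted beats, IAc = (1/4) Σ [1 − |R − C|/R].
- Perfect counting (C = R): 1, the ceiling.
- Nothing counted (C = 0): 0.
- Counting 1.5 times the beats: 1 − 0.5 = 0.5, still positive.
- Counting 2.2 times the beats: 1 − 1.2 = −0.20.
- Counts of 80, 90, 100, 110 against 35, 41, 47, 53: (−0.286 − 0.195 − 0.128 − 0.075)/4 = −0.171.

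Over-counting therefore takes IAc to 0 or below only when counts average about twice the recorded beats or more.

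**3. How likely a zero is**

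The documents give no score distribution, so the share scoring zero, p, is assumed. With 32 participants (Sample size), the chance of at least one zero at a time point is 1 − (1 − p)^32.

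| p (assumed) | expected zeros, 32p | chance of at least one |
|---|---|---|
| 0.02 | 0.64 | 0.48 |
| 0.05 | 1.6 | 0.81 |
| 0.10 | 3.2 | 0.97 |
| 0.20 | 6.4 | 0.999 |

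If zeros are dropped, the mean of the remainder is mean/(1 − p). In simulated right-skewed DASS subscales (negative binomial, assumed):
- mean 4.0 with p = 0.334 becomes 4.0/0.666 = 6.0;
- mean 6.0 with p = 0.193 becomes 6.0/0.807 = 7.4;
- mean 8.0 with p = 0.142 becomes 8.0/0.858 = 9.3.

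**4. Adding a constant**

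A DASS change from 4 to 0 on the scale ln(x + c) is ln(c) − ln(4 + c), compared here with a change from 14 to 10.

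| c | 4 to 0 | 14 to 10 |
|---|---|---|
| 0.01 | −5.99 | −0.34 |
| 0.5 | −2.20 | −0.32 |
| 1 | −1.61 | −0.31 |
| 2 | −1.10 | −0.29 |

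Both are drops of 4 points. The second barely depends on c, while the first depends on it heavily.

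**5. Left skew**

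IAc was simulated with assumed Beta shapes, n = 32 for the Shapiro-Wilk test.

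| shape | mean | skewness raw | skewness after log | rejection raw | rejection after log |
|---|---|---|---|---|---|
| Beta(3,1.5) | 0.67 | −0.51 | −1.66 | 0.31 | 0.89 |
| Beta(4,2) | 0.67 | −0.47 | −1.44 | 0.20 | 0.79 |
| Beta(5,2) | 0.71 | −0.60 | −1.44 | 0.30 | 0.79 |
| Beta(6,2) | 0.75 | −0.69 | −1.42 | 0.37 | 0.81 |
| Beta(8,2) | 0.80 | −0.82 | −1.42 | 0.50 | 0.78 |

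For each shape, the log moves the data further from normality.

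**The case against.** The strongest defence is that this is a journal article, and that a constant for zeros is a detail left to a fuller document. That would answer silence, but the article states an explicit rule without exceptions, and followed literally it gives undefined values. A constant is also not neutral, as step 4 shows.

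Several stronger readings are tempting but not supported:
- *Zeros are certain.* The documents give no distributions. The plan lists one ANCOVA per questionnaire and does not settle whether totals or subscales are analysed. A DASS total of 0 needs all 21 items at 0, so zeros are mainly a subscale risk.
- *Best scores will be replaced by imputed values.* An observed 0 is not missing. This would require that no constant is used, that undefined logs become missing in SPSS, and that imputation follows transformation. The protocol states none of these.
- *Those altered are the participants who are well.* This fits DASS only. A MAIA-2 score of 0 means answering never throughout, and an IAc of 0 is poor accuracy.
- *Ordinary over-counting breaks IAc.* The −0.171 example means reporting about 147 to 160 beats per minute against about 70 recorded, which is extreme.
- *The normality test will fire at one time point or in one arm only.* The protocol does not specify testing by arm or by time point, nor a significance level, so rejection rates at 8 per arm describe a procedure it does not set out.

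It is also fair to say that the log is a reasonable choice for RMSSD and LF/HF; the fault lies in applying it to everything.

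**Conclusion.** The point holds as a defect in a stated rule. From the protocol's own item ranges and formula, the log is undefined for DASS and MAIA-2 scores of 0 and for IAc at or below 0. That part needs no assumption beyond such values occurring and the outcome being judged skewed. Their frequency is unknown; at an assumed 2% to 10% zeros, the chance of meeting at least one among 32 runs from 0.48 to 0.97. Loss or imputation of these scores is a conditional consequence.

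The worsening of skew in IAc rests on the assumption that IAc is left-skewed. Its ceiling of 1 makes this plausible, but no distribution is given.

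PANAS-SF, AAQ-II and SACS are free of the zero problem. Feasibility and acceptability are the primary outcomes, and everything affected is secondary, so the impact is moderate: worth correcting, with no threat to the study's main purpose.

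**What to change.** Replace the data-driven rule with a scale fixed in advance for each outcome and used at both time points:
- RMSSD and LF/HF ratio (strictly positive): natural log, with effects back-transformed and reported as ratios.
- All questionnaire scores and IAc: raw scale, so that zero and negative values remain ordinary observations.
- Assumptions: examine the residuals of the fitted models in place of a normality test on the raw data. If residuals are clearly non-normal, add a robust or bootstrap sensitivity analysis. With about 8 participants per arm, bootstrap intervals are themselves imprecise, so they should support the main analysis and not replace it.

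The cost is a change of wording and slightly more analysis work. No new data are needed. HRV effects would be expressed as ratios instead of differences.

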### Objectives

This study aims to investigate the feasibility and acceptability of four osteopathic interventions for adults with mild to moderate mental health symptomatology. A secondary aim is to evaluate the influence of these four interventions on physiological factors including HRV and interoception. The study will aim to evaluate their effectiveness in improving psychological outcomes including depression, stress, anxiety, negative affect (NA) and psychological flexibility. It is first hypothesised that the interventions will be feasible and acceptable to participants. It is also hypothesised that the interventions will induce psychophysiological relaxation by significantly increasing HRV and improving IAc. No specific predictions are made about blood pressure (BP) as data on this is only being collected to check that we are within safe BP bounds, that is, for participant safety. A final hypothesis is that the four interventions will lead to similar improvements in depression, anxiety, stress and NA.

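### The assessor is masked to arm, but nothing hides the time point while HRV artefacts are removed, so the uncontrolled pre-to-post HRV effect is left unprotected at that step

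*Protocol article*

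**What the plan says.** All references are to the protocol article.

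- **Hypothesis (Objectives).** The prediction is that the "interventions will induce psychophysiological relaxation by significantly increasing HRV and improving IAc". The strengths and limitations box states that the study has no control group.
- **Artefact handling (Statistical methods, Outcomes).** "HRV data will be preprocessed, and inspected for any potential artefacts, and these will be removed if identified". Then "RMSSD will be calculated on the preprocessed artefact removed data using Kubios V.3.5". The HRV model uses RMSSD and the LF/HF ratio.
- **Masking (Blinding).** After the baseline measures, "the outcome assessor will leave the room (to ensure blinding) and the intervention will begin, conducted by the osteopath". Participants are asked not to tell the assessor which treatment they had. The assessor is also the analyst, and the arm stays hidden throughout that work: "the random numbers corresponding to each group will only be revealed when this analysis has been completed".
- **Access (Data management).** The data sit in a folder "which only the outcome assessor will have access to for the duration of the study". The Confidentiality and Access to data sections likewise limit access to one researcher. No second reader is described.

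The article does not say how HRV files are labelled when they are opened for cleaning, and no section hides the time point.

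**The concern.** The safeguard and the claim do not match. Withholding the group codes keeps the analyst from favouring one arm over another. The HRV hypothesis is not about one arm over another: it is a Time effect in all participants, with no untreated group to subtract. A person who was present for the baseline recording, holds all the files and also analyses them can be expected to know which recording is which, unless something prevents it.

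Deciding whether a beat is an artefact can involve judgement, and RMSSD is built from squared successive differences, so one abnormal interval weighs heavily. If such judgements lean differently before and after treatment, an HRV rise can be created or hidden. At stake are the HRV effect size, which the Discussion part of the abstract offers as preliminary evidence of benefit, and the exploratory correlation of RMSSD change with DASS change.

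**Working it through.** **Inputs from the article.** Recordings of at least 5 minutes at two time points (Heart rate variability); 32 participants, 8 per arm (Sample size; the abstract says 30, which does not affect this point). The article gives no RMSSD mean, SD, expected change or artefact rate, so there is no HRV figure to reproduce.

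**Assumptions, not from the article.** Heart rate 60 to 75 bpm; clean RMSSD 20 to 60 ms; the beat types below.

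**Step 1: one beat in one record.** RMSSD_new = √(RMSSD² + SS/(beats − 1)), where SS is the sum of squares added by the beat. With RR the mean interval, SS is
- 2·RR² for one missed R-peak
- 2·(RR/2)² for one extra detection
- 6·(p·RR)² for one beat early by a fraction p with a full pause (successive differences −d, +2d, −d)

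At 75 bpm (RR 800 ms, 375 beats) and clean RMSSD 30 ms:
- missed: √(900 + 1,280,000/374) = 65.7 ms (×2.19)
- extra: √(900 + 320,000/374) = 41.9 ms (×1.40)
- 20% early: √(900 + 153,600/374) = 36.2 ms (×1.21)

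Over the whole assumed range, the ratio runs from ×1.06 (20% early, 75 bpm, 60 ms) to ×4.21 (missed, 60 bpm, 20 ms).

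**Step 2: a 30%-early beat carried to the group.** Take RR 850 ms and 350 beats: SS = 6 × 255² = 390,150, and SS/349 = 1,118. Suppose the beat is removed before treatment but left in afterwards in 3 of 32 participants, who all share the clean value shown.

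| Clean RMSSD | With the beat | Change | × 3/32 |
|---|---|---|---|
| 20 ms | 39.0 ms | +95% | 8.9% |
| 34 ms | 47.7 ms | +40% | 3.8% |
| 54 ms | 63.5 ms | +18% | 1.7% |

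Simulated series gave +92% in the first row, hence 8.6%. With 6 of 32, the middle row gives 7.5%. A 20%-early beat at 34 ms gives √(1,156 + 173,400/349) = 40.7 ms, or +20%, which is about half the middle row.

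**Step 3: against noise.** Assume SD of ln RMSSD 0.5 and pre-post correlation 0.8. The SE of the mean log change at n = 32 is 0.5 × √(2 × 0.2)/√32 = 0.056. The middle-row shift on the log scale is ln 1.40 × 3/32 = 0.032, or 0.6 SE; with 6 of 32 it is 0.063, or 1.1 SE. Setting the percentages directly against 5.6% gives 0.7 and 1.3.

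**Step 4: false significant rise.** A paired t test stands in for the Time effect: two-sided 5%, n = 32, no true change, 75 bpm, geometric mean RMSSD 30 ms, log scale, 20,000 simulations. Only post records keep the beat.

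| Post records affected | Missed R-peak | 20%-early beat |
|---|---|---|
| none | 2.3% | 2.3% |
| exactly one of 32 | 4.4% | 3.1% |
| 10% | 17% | 6% |
| 20% | 48% | 12% |
| 30% | 78% | 21% |

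One missed beat in one record moves mean change by only 35.7/32 = 1.1 ms, and the outlier also inflates the SD. LF/HF was not simulated.

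**The case against.** The strongest reply has four parts.

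- **Time-point knowledge is not stated.** Correct. It is inferred from the assessor's role and from silence on file labelling. The article does not exclude hidden labels.
- **Inspection need not mean discretion.** The sentence does not say the inspection is visual and does not rule out an automatic rule; as written it covers all recordings alike. Thresholds and correction algorithms are also details that an article may leave to a fuller document. This stands: the lack of a stated threshold is not the fault here. What remains is the masking that the article does describe, which does not cover the effect that it hypothesises.
- **The size depends on a chosen scenario.** Nothing in the article suggests that obvious artefacts would be left in one set of recordings, always in the same direction. A missed R-peak makes an interval of nearly double length and is hard to overlook, so the largest error rates are the least likely. This stands, and the figures are illustrations.
- **Other threats are larger.** Rest and repeated measurement already confound an uncontrolled Time effect, HRV is secondary, and low power is acknowledged. True; this limits the weight of the point but does not answer it.

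A reader might also infer that a single beat can drive the trial's HRV result. It can drive one participant's RMSSD; with 32 participants, the false-rise rate goes only from 2.3% to 4.4%.

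**Conclusion.** The point holds in a limited form. The masking described for the assessor is to arm, the HRV hypothesis is an uncontrolled Time effect, and one person measures, holds, cleans and analyses the data with no step that hides the time point. Arm masking cannot protect that effect during artefact removal.

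The possible size is large for one participant (about 6% to more than 100% of RMSSD). It is modest for the group unless cleaning is uneven in one direction across several records: about 1.7% to 9% of mean RMSSD with a 30%-early beat in 3 of 32. All sizes rest on assumed heart rate, clean RMSSD, variability and beat type. The documents do not support reading this as evidence that biased cleaning will occur.

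No feasibility or acceptability conclusion changes. Only the HRV effect sizes, their significance and the correlations built on them are affected. Minor to moderate.

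**What to change.** In Statistical methods, Outcomes, add that:

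1. before any artefact inspection, a script renames all HRV recordings (32 × 2 = 64 files) with random codes that hide time point as well as arm, including any recording time visible in the file;
2. one artefact rule, set before any file is opened, is applied identically to every file;
3. the codes are linked back to time point only after RMSSD and LF/HF have been exported;
4. the percentage of beats corrected is reported at each time point.

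The cost is a short script and a few sentences, with no extra staff, visits or measurements. Switching to automatic correction alone is a less certain remedy: the article does not describe what the software offers, and if HRV truly rises, a fixed threshold could remove more genuine beats after treatment than before. Hiding the time point is therefore the main change. It does not remove rest or repeat-measurement effects, which the report should still acknowledge.
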